### 2.7. Outcome indicators

#### 2.7..1. Primary outcome indicator.

24-hour urinary protein quantification, which will be measured at baseline, weeks 8 and 12 of treatment, and weeks 12 and 24 of follow-up.

#### 2.7..2. Secondary outcome indicators.

Kidney function, which will be measured at baseline, weeks 8 and 12 of treatment, and weeks 24 of follow-up.The TCM Syndrome score, which is a comprehensive record of symptoms associated with DKD, includes blurred vision, turbid urine, fatigued spirit, lack of strength, tinnitus, dizziness, spontaneous sweating, night sweats, constipation, soreness of the low back and knees, soreness of the low back and knees. At baseline, weeks 8 and 12 of treatment, and weeks 24 of follow-up, the researchers will evaluate each of the 4 levels according to the above content, as detailed in Table 2.Safety assessments, including routine blood tests, urinalysis tests, liver function, and electrocardiographic results. These measures will be collected at baseline, 8 and 12 weeks of treatment, and 24 weeks of follow-up. Patients will be asked to record any unwell symptoms that occur during the study, and details of all adverse events will be recorded in a case report form.

**Table 2 T2:** TCM symptom scoring standard.

TCM symptoms	Scoring criteria
Blurred vision	0 None
	2 The vision is not clear
	4 Blurred vision relatively difficult to distinguish objects
	6 Blurred vision difficult to distinguish objects
Turbid urine	0 None
	2 Proteinuria ±~+
	4 Proteinuria ++
	4 Proteinuria +++
Lack of strength	0 None
	1 Loss of energy after tiredness, easy recovery after rest, can insist on light manual labor
	2 Mentally tired, difficult to recover after rest, barely insist on daily work
	3 Mentally tired, unable to recover after rest, unable to persist in daily work
Tinnitus	0 None
	1 Occasional tinnitus, low ringing, intermittent
	2 Intermittent tinnitus, such as cicadas, low in the day and loud at night, can be reduced by pressing
	3 Persistent tinnitus, such as tide, continuous attacks, not reduced
Dizziness	0 None
	1 Occasional dizziness
	2 Dizziness often occurs and is tolerable
	3 Persistent dizziness
Spontaneous sweating	0 None
	1 Skin tide
	2 Wet skin
	3 Sweat out
Constipation	0 None
	1 Head sweating, occasional
	2 The chest and back are wet and recurring
	3 The whole body is wet like washing, often appears
Soreness of the low back and knees	0 None
	1 Occasionally, worse after working, can sit for a long time
	2 Often feel weak and weak in the waist, weak legs, and not sitting for a long time
	3 Back and knee soreness, unable to sit and walk
Thirst with liking for fluids	0 None
	1 Thirst, relieved after drinking water, increase daily drinking water by more than 1/2 times
	2 Thirst is obvious, drink less than 4000ml daily, or increase by 1–2 times
	3 Dry mouths, no relief after drinking water, daily drinking water volume > 4000 mL, or increase > 1 time

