## 2. Materials and methods

### 2.1. Study design

This is a prospective randomized controlled trial to investigate the efficacy and safety of warm acupuncture in the treatment of type 2 DKD. The patients who meet the criteria will be randomly divided into the treatment group and the control group. According to the recommendations of clinical guidelines, the 2 groups of patients will be treated with conventional Western medicine, and the treatment group will be treated with warm acupuncture in addition, follow up for 24 weeks after 12 weeks of continuous treatment. Flow diagram is shown in Fig. 1, and study schedule is shown in Table 1. This experiment will follow the Standards for Reporting Interventions in Clinical Trials of Acupuncture^[13]^ and the comprehensive trial report standard.^[14]^ The study will be completed under the guidance of Standard Protocol Items: Recommendations for Interventional Trials (SPIRIT checklist) 2013 statement.

**Table 1 T1:** Study schedule.

Stage project	Screening period	Treatment period		Follow-up	
	Baseline	8 wk	12 wk	12 wk	24 wk
Record fill	√				
Fulfill inclusion criteria and exclusion criteria	√				
Sign informed consent	√				
Random allocation	√				
Treatment	√	√	√		
Effectiveness observation					
24-hr urinary protein quantification	√	√	√	√	√
Kidney function	√	√	√		√
The TCM Syndrome score	√	√	√		√
Safety assessments					
Routine blood tests	√	√	√		√
Blood test and urinalysis	√	√	√		√
Liver function	√	√	√		√
Electrocardiographic	√	√	√		
Record of adverse event		√	√	√	√

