### 2.6. Interventions

Basic treatment: treatment protocols will be developed based on the basic treatment principles established by the *2012 American Diabetes Association Practice Guidelines*,^[7,17]^ as follows: provision of health education, such as diet and exercise guidance; glycemic control; biguanides will be used in patients with obesity and/or eGFR higher than 60 mL/min/1.73 m^2^; nonobese patients and/or patients with eGFR below 60 mL/min/1.73 m^2^ will receive glinide drugs. When blood glucose control is not ideal, choose 2 oral drugs or insulin supplementation. Hemoglobin A1c (HbA1c) will be controlled below 9.0%; blood pressure control: angiotensin-converting enzyme inhibitors/angiotensin receptor blockers will be recommended. For patients whose blood pressure cannot be controlled to 140/90 mm Hg with angiotensin-converting enzyme inhibitors/angiotensin-receptor blockers, nondihydropyridine calcium channel blockers will be added, and diuretics and/or beta blockers will be added. Blood pressure will be controlled to 140/90 mm Hg or less in all patients; blood lipid control: select statins or fibrates based on blood lipid of patients.

Warm acupuncture treatment: patients will be in a sitting position, and 75% alcohol will be used to disinfected the acupuncture site. The acupuncture points are Shenshu (BL 23), Sanyinjiao (SP 6), Taixi (KI 3), Xuehai (SP 10), Pishu (BL 20), Zusanli (ST 36) and Guanyuan (CV 4), acupoint positioning is based on the positioning standards in the *National Standards of the People’s Republic of China*.^[18]^ Disposable stainless steel acupuncture needles (0.25mm × 40mm, Suzhou Hualun Medical Appliance Co., Ltd, Suzhou, China) will be used and operated by an acupuncture-moxibustion practitioner with 3 years of clinical experience. After arrival of qi, a 27-mm piece of moxa stick (Nanyang Baicaotang Co., Ltd, China, size: 18 mm × 27 mm) will be added to the handle of the needle. The bottom of the moxa stick is about 20 mm away from the skin, and the pad is separated by a small piece of paper. The bottom of the moxa section will be ignited, and the treatment will be finished after the moxa sticks was burned out. The treatment will be given for 30 minutes each time, once every other day.

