The patients in the treatment group will receive basic treatment combined with warm acupuncture, while the patients in the control group only receive basic treatment. Both groups will continue to receive standard treatment for 12 weeks.

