## 3. Discussion

DKD is a serious microvascular complication, which is caused by long-term diabetes or poor blood glucose control, and is also an important factor in the death of diabetic patients.^[19]^ The pathogenesis of DKD is complex, and the early symptoms are occult. Therefore, clinical attention should be paid to the treatment and control of DKD.^[20]^

The pathogenesis of DKD is complicated. In recent years, the theory of autophagy has been widely used in the study of metabolic diseases, and it has been found that it is closely related to the damage of target organs. Autophagy is an important life phenomenon of living organisms; however, if autophagy is abnormally activated due to environmental stress and other factors, its autophagy expression beyond a certain physiological range will in turn cause damage to target cells, thus causing damage to target organs. The occurrence of diabetic kidney damage is closely related to the abnormal activity of autophagy and directly related to the degree of urinary protein.^[15]^ Western medicine treatment is mainly aimed to control the risk factors and further control the progress of the disease, but the clinical efficacy is still not satisfied.^[21]^

Studies have confirmed that the bidirectional regulation of acupuncture and moxibustion has something in common with the bidirectional regulation of autophagy expression. Acupuncture and moxibustion can effectively reduce urinary microprotein excretion, alleviate kidney injury and improve renal function in patients with early DKD.^[21,22]^ Warm acupuncture is a further development of acupuncture, clinical studies have shown which can reduce blood viscosity, improve microcirculation, regulate immune function, and inhibit platelet aggregation.^[23]^ Although evidence has shown that warm acupuncture is beneficial for patients with DKD, whether it can be used as a complementary or alternative treatment regimen for DKD remains controversial. We will use this study to investigate the clinical efficacy of warm acupuncture in the treatment of DKD, which is beneficial for both patients and clinical decision makers.

There are also some shortcomings in this study: due to the factors of treatment methods, this study could not achieve double blindness, which may have some impact on the study results; at the same time, there may be population regionalization in the study.

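### The comparison of symptomatic adverse events is at risk of unequal ascertainment: about 42 practitioner sessions in one group, two listed treatment-period visits in the other

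*Protocol article*

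**What the plan says.** Safety is a stated aim of the trial alongside efficacy (Abstract; section 2.1).

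- **Source of symptomatic events.** Section 2.7.2: "Patients will be asked to record any unwell symptoms that occur during the study". The remainder of that sentence covers documentation, for every event whatever its source: "details of all adverse events will be recorded in a case report form".
- **Scheduled recording.** The row "Record of adverse event" in Table 1 is ticked at treatment weeks 8 and 12 and follow-up weeks 12 and 24. The columns are the same for both groups.
- **Scheduled tests.** For routine blood tests, urinalysis, liver function and ECG, section 2.7.2 says: "These measures will be collected at baseline, 8 and 12 weeks of treatment, and 24 weeks of follow-up". Table 1 has no ECG tick at follow-up, but neither place separates the groups.
- **Contact in the acupuncture group.** Section 2.6: "The treatment will be given for 30 minutes each time, once every other day". Section 2.1 sets the period: "follow up for 24 weeks after 12 weeks of continuous treatment".
- **Contact in the control group.** Section 2.6: "while the patients in the control group only receive basic treatment". No sham or attention-matched session is described.
- **Blinding.** The Discussion concedes that "this study could not achieve double blindness". Section 2.5 states masking for efficacy assessors and does not mention those who record adverse events.
- **Analysis.** Section 2.9 puts safety data in the safety set and names the chi-squared test, at the 0.05 level, for count data.

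**The concern.** A symptom has to be noticed, remembered and mentioned before it reaches the case report form. One group has a practitioner at hand every second day; the other has few listed occasions. Each session is a chance for a patient to mention a symptom, be reminded of one, or have a reaction seen.

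The text leaves two ways to run this, and each has a weakness. If remarks and observations at sessions go onto the form, which the rule that all adverse events are recorded would allow, the two groups are observed with different intensity and a difference in counts mixes harm with opportunity to report. If sessions are not used in this way, burns, bleeding or fainting at needle and moxa sites have no systematic capture, because none of the scheduled tests can show them.

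At stake is how the adverse-event table can be read. An excess in the acupuncture group could be real or produced by contact, and the data could not separate the two afterwards.

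**Working it through.** **1. Contact count**

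Inputs: 12 weeks of treatment (section 2.1), one session every other day (section 2.6), visit columns in Table 1.

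- Treatment period: 12 × 7 = 84 days.
- Sessions in the acupuncture group: 84 / 2 = 42.
- Sessions by the end of week 8: 56 / 2 = 28.
- Treatment-period visits listed after baseline, in both groups: 2 (weeks 8 and 12).

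The listed contacts are therefore about 42 sessions, with the two visits on session days or in addition, against 2 visits in the control group. This counts listed contacts only. Basic treatment in section 2.6 includes health education and stepwise control of glucose, blood pressure and lipids, which implies further clinic contact that the article does not count and that may occur in both groups.

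**2. What is alike and what differs**

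| Element | Acupuncture | Control |
|---|---|---|
| Patient's own symptom record | yes | yes, same instrument |
| Adverse-event ticks in Table 1 | weeks 8, 12; follow-up 12, 24 | same |
| Blood, urine, liver, ECG | one schedule | same |
| Practitioner sessions | about 42 | none |
| Patient blinded | no | no |
| Stated step to equalise ascertainment | none | none |

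**3. How much could it matter?**

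The document gives no adverse-event rate and no detection probability, so there is no figure of the plan's own to reproduce and the bias cannot be computed. The following is an illustration on assumed values: the same true risk in both groups (20% to 40%), 42 patients per group (section 2.4), and detection probabilities chosen to span a small to a large gap.

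- Observed risk = true risk × detection probability.
- Observed risk ratio = ratio of the detection probabilities, since the true risk cancels.
- Rejection = exact binomial probability that a two-sided chi-squared test without continuity correction gives P < .05.

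| Detection, acupuncture v control | Observed risks, true risk 20% | Observed risks, true risk 40% | Risk ratio | Rejection over true risks 20% to 40% |
|---|---|---|---|---|
| 100% v 100% | 20% v 20% | 40% v 40% | 1.0 | 5% to 6% |
| 90% v 80% | 18% v 16% | 36% v 32% | 1.12 | 6% to 7% |
| 90% v 60% | 18% v 12% | 36% v 24% | 1.5 | 12% to 22% |
| 90% v 50% | 18% v 10% | 36% v 20% | 1.8 | 19% to 38% |

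In patients, the smallest gap at 20% true risk is 0.02 × 42 = 0.8 patients, and the largest gap at 40% is 0.16 × 42 = 6.7 patients. With a small detection gap the effect is negligible; with a large one it is material. The document does not say where in this range the trial would lie.

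**The case against.** The case against is substantial, and several stronger readings that a reader might infer do not survive it.

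- **That the comparison is biased.** The patient record is the same instrument in both groups, runs through the study and does not depend on visits. The document nowhere says that sessions are used to elicit adverse events. Only a risk of bias can be asserted.
- **That events are captured only from patients' notes.** Section 2.7.2 also says that all adverse events go on the form, so a burn seen by the practitioner is eligible. What is missing is a stated check at each session, not permission to record.
- **That control patients must recall symptoms over eight weeks.** Being asked to note symptoms as they occur reads more naturally as an ongoing record. Table 1 does not say that recording is retrospective.
- **That actual contact is 21 to 1.** 42 / 2 = 21 is a ratio of listed contacts; those under basic treatment are uncounted.
- **That every symptom is affected alike.** Dizziness, for example, is graded by researchers in both groups on one schedule as part of the TCM syndrome score (Table 2), so it is asked about systematically whatever the group.

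Two general objections remain. The article condenses a fuller protocol, and question wording or session checklists may sit there. That is fair, and the point does not rest on their absence: it rests on how the stated source, visit schedule and contact pattern combine. It can also be said that closer observation would overstate harms of acupuncture, which is the cautious direction. That is a reasonable comfort for general symptoms, but it does not help a reader interpret an excess, and it says nothing about local harms.

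**Conclusion.** The between-group comparison of symptomatic adverse events is at risk of unequal ascertainment, most likely towards more recorded events in the acupuncture group. This rests on stated facts: about 42 sessions against two listed treatment-period visits, self-recorded symptoms, patients who know their treatment, and no stated step that makes elicitation alike. Laboratory and ECG findings are not affected by the contact imbalance, but they cannot stand in for local needle and moxa harms.

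The size is unknown. The range in the illustration depends wholly on assumed detection probabilities and true risks, and it includes a near-null case. The chi-squared figures further assume that the general rule for count data in section 2.9 is applied to adverse events. The document supports a modest, inexpensive improvement; it does not support calling the safety conclusion unsound.

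**What to change.** In section 2.7.2:

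1. State that adverse events are elicited with the same non-leading questions in both groups at the visits already in Table 1 (treatment weeks 8 and 12, follow-up weeks 12 and 24), and that the between-group comparison is based on these responses. The patient's own record can be brought to the visit to support the answers.
2. Have the practitioner log local events (such as burn, bleeding, infection or fainting) on the case report form at each session.
3. Report events first noted at sessions separately for the acupuncture group, per patient and per session, outside the between-group test. Keep all events, however detected, in the safety-set listing.

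**Cost.** One page of the case report form, a few sentences in 2.7.2 and a short entry at each session; no extra visits or staff. Some events are left out of the formal comparison, although they are still reported.

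**What it does not cure.** Patients remain unblinded, and frequent sessions may still make acupuncture patients readier to report at the scheduled visits. This belongs with the limitations in the Discussion, next to the lack of double blinding. The change has to be made before data collection, because the manner of elicitation cannot be reconstructed afterwards.

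### Table 2, which defines the secondary TCM Syndrome score, is wrong as printed in three of its nine rows and does not match the item list in section 2.7.2

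*Protocol article*

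**What the plan says.** The TCM Syndrome score is a secondary outcome (protocol article, section 2.7.2), rated at baseline, weeks 8 and 12 of treatment, and week 24 of follow-up. The text ties the rating to the table: "the researchers will evaluate each of the 4 levels according to the above content, as detailed in Table 2".

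The symptom list in the running text ends with "spontaneous sweating, night sweats, constipation, soreness of the low back and knees, soreness of the low back and knees", so the last symptom is named twice.

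Table 2 prints the following:

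- **Turbid urine.** The level 3 and level 4 entries both begin "4 Proteinuria", one followed by ++ and the other by +++. The only other row scored in steps of two, blurred vision, ends at "6 Blurred vision difficult to distinguish objects".
- **Constipation.** Level 1 is "1 Head sweating, occasional", level 2 is "2 The chest and back are wet and recurring", and level 3 describes drenching of the whole body.
- **Thirst.** Level 1 needs an increase in drinking of more than half, with no upper limit. Level 2 is under 4000 mL a day or an increase of 1 to 2 times. Level 3 includes "daily drinking water volume > 4000 mL, or increase > 1 time".

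**The concern.** A rating scale works only if each item measures what its label says, its levels exclude one another, and the items that make up the total are fixed. Table 2 fails each of these at some point, and the document names no source scale that would settle the matter.

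A rater who follows the table enters sweating under the label of constipation, and has to choose between levels for some patients with thirst. A patient who moves from +++ to ++ shows no change on turbid urine. A reader of the results could not tell from the text which symptoms the total contains or what range it has. If the case report form reproduces the table, information that was never recorded, such as bowel symptoms, cannot be recovered at analysis.

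**Working it through.** The plan states no total or range for the score, so there is no figure to reproduce. The check compares the text of section 2.7.2 with Table 2.

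**1. Item sets**

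| | Items |
|---|---|
| Text, entries | 11 |
| Text, distinct (low-back and knee soreness appears twice) | 11 − 1 = 10 |
| Table 2, rows | 9 |
| In both | 8 |
| Text only | 10 − 8 = 2 (fatigued spirit, night sweats) |
| Table only | 9 − 8 = 1 (thirst) |

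**2. Distinct scores per row**

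Turbid urine is scored 0, 2, 4, 4: four grades but three values. Every other row has four values. One of the three upward steps in this row, from ++ to +++, therefore carries no weight.

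**3. Constipation**

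Levels 1 to 3 refer to the head, the chest and back, and the whole body, all in terms of sweating or wetness. None concerns bowel function, so the only level that can be applied to constipation is 0 (none). Night sweats, listed in the text immediately before constipation, has no row.

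**4. Thirst**

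Take an increase of 1.5 times:

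- Level 1: 1.5 > 0.5, met (increase criterion only).
- Level 2: 1 ≤ 1.5 ≤ 2, met.
- Level 3: 1.5 > 1, met (increase criterion only).

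Any increase above 1 and up to 2 times meets the increase criterion of both level 2 and level 3. On volume, level 2 is below 4000 mL and level 3 above it, so exactly 4000 mL falls in neither.

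**5. Range of the total**

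| Version | Arithmetic | Maximum |
|---|---|---|
| Table 2 as printed | 6 + 4 + 7 × 3 | 31 |
| Table 2, if turbid urine ran 0/2/4/6 like blurred vision (assumption) | 6 + 6 + 7 × 3 | 33 |
| The 10 items in the text, if the two without a row were scored 0 to 3 (assumption), turbid urine to 4 | 6 + 4 + 8 × 3 | 34 |
| The same, turbid urine to 6 | 6 + 6 + 8 × 3 | 36 |

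The document does not say which of these applies.

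**6. Share of the score affected**

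The faulty rows (turbid urine, constipation, thirst) can contribute 4 + 3 + 3 = 10 of 31 points, about 32%. The six usable rows (blurred vision, lack of strength, tinnitus, dizziness, spontaneous sweating, soreness) contribute 6 + 5 × 3 = 21 of 31, about 68%.

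**The case against.** The best defence is that these are clerical slips in one table. The constipation label over sweating text, with night sweats and constipation adjacent in the list, looks like two rows collapsed into one, perhaps in typesetting, translation or reading the PDF. The case report form is not shown and may be correct. That could explain the constipation row. It cannot explain the repeated score of 4, the thirst overlap, or the running-text list, which names one symptom twice and omits thirst.

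Parts of the defence stand:

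- Fatigued spirit may be meant to fall under lack of strength, whose levels 2 and 3 mention mental tiredness. The document does not say so. If it does, one mismatch disappears; night sweats and thirst remain.
- The text asks for four levels per item, and turbid urine has four printed levels. It does not expressly require four different scores, so the tie could be intended, though nothing says it is.
- Thirst levels 1 and 3 also differ in whether drinking brings relief, so a rater has more to go on than the size of the increase. Level 2 says nothing about relief, so the overlap between levels 2 and 3 is not fully resolved.
- The same table applies to both arms, and section 2.5 keeps efficacy assessors unaware of allocation. Lost sensitivity and ambiguity are shown; bias in favour of one arm is not.

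Four stronger readings are tempting, and the document does not support them:

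- **The whole score is invalid.** Six of nine rows have ordered, usable levels.
- **Sweating is counted twice.** The text lists spontaneous sweating and night sweats as separate symptoms. If the misplaced descriptors belong to night sweats, two sweating items are what the text describes.
- **Grading turbid urine by proteinuria improperly re-counts the primary outcome.** This is a design choice that contradicts nothing in the document.
- **The tied grades are the common ones in this trial, because eligibility requires 0.5 to 3.5 g of urinary protein per 24 hours.** The document gives no link between + grades and grams per day, so the frequency is unknown.

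**Conclusion.** The point holds as an internal error in the definition of a secondary outcome. Three of nine rows, carrying 10 of 31 points, are wrong or ambiguous as printed: constipation cannot be rated, one step of turbid urine scores nothing, and thirst levels 2 and 3 are not mutually exclusive. The item list in the text shares 8 items with the table, has 2 of its own and lacks 1. The total as printed is therefore not the instrument the text describes.

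The primary outcome, 24-hour urinary protein, and the sample size built on it are untouched. The point should be fixed; it does not threaten the trial's main conclusion.

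The counts and the maximum of 31 come directly from the document. The maxima of 33 and of 34 to 36 rest on the assumptions stated with them. Which item set and which scores were intended cannot be decided from the document.

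**What to change.** Before the first rating, reconcile Table 2, the item list in section 2.7.2 and the case report form so that they agree:

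- Give constipation bowel descriptors, and decide where the sweating descriptors now in that row belong.
- Give every listed symptom its own row, or state that it is merged with another. Settle whether fatigued spirit, night sweats and thirst are in the score, and remove the repeated soreness entry.
- Give proteinuria ++ and +++ different scores, or state that the tie is intended.
- Make the thirst levels mutually exclusive, and cover exactly 4000 mL.
- State the resulting number of items and the range of the total.

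The cost is a correction to one table, one sentence and one form page, with the ethics committee review that section 2.8 requires for protocol changes. If rating has already begun, report which version of the form was used and whether item-level scores were kept.
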